## Abstract

**Question:**

Is internet-delivered cognitive behavior therapy implemented within a stepped care model noninferior to, and cost-effective compared with, face-to-face cognitive behavior therapy for pediatric obsessive-compulsive disorder?

**Findings:**

This protocol describes a multicenter randomized clinical noninferiority trial conducted in a health care setting. Participants are 152 children and adolescents aged 7 to 17 years.

**Meaning:**

This trial will add to the current knowledge base by specifically evaluating a stepped care approach to the treatment of pediatric obsessive-compulsive disorder in which patients are first offered internet-delivered cognitive behavior therapy as a low-intensity intervention, reserving higher-intensity treatments such as face-to-face therapy for those who do not benefit from the first step.

## Introduction

Cognitive behavior therapy (CBT) is regarded as the gold-standard treatment for pediatric obsessive-compulsive disorder (OCD)^1,2^ and has consistently shown large effect sizes compared with both wait-list (*g* = 1.53) and various active comparators (*g* = 0.93)^3^ as well as sustained long-term effects.^4^ Furthermore, CBT is an effective augmentation treatment for patients showing suboptimal response to initial courses of both serotonin reuptake inhibitors^5^ and CBT.^6^ Unfortunately, suitably trained CBT therapists specializing in OCD are scarce and typically concentrated in large urban areas, and it is estimated that many patients do not have access to CBT.^7,8,9,10^ One way to increase the availability of CBT is to remotely deliver it online without the need to attend in-clinic sessions with a therapist.^11^ Our research group has developed a therapist-guided internet-delivered CBT (ICBT) program for youth with OCD called *BIP OCD*. The treatment is primarily self-guided, with assistance from parents or legal guardians, and supported by a designated therapist who communicates with both the child and the parent through the entire treatment. The BIP OCD program has to date been evaluated in 2 open pilot studies in both children^12^ and adolescents^13^ that showed high acceptability and safety and promising results. A subsequent randomized clinical trial including 67 patients demonstrated superiority and cost-effectiveness of BIP OCD against a wait-list control.^14,15^ Interestingly, the effects of ICBT were slightly weaker than expected but continued beyond the primary end point, with patients experiencing additional symptom improvement at the 3-month follow-up. This delayed improvement phenomenon has also been observed in other ICBT trials.^16,17^ As participants in these trials were primarily self-referred^12,13,14^ and may therefore constitute a selected group of individuals (eg, highly educated, more motivated), the generalizability of these findings to regular clinic-referred patients is currently unclear.

Before ICBT for pediatric OCD can be recommended for implementation in routine clinical care, it is essential to evaluate whether this approach is comparable or noninferior and cost-effective compared with the gold standard of face-to-face CBT. Even if ICBT were less efficacious than face-to-face CBT, it might still have a meaningful place in the health system, as its potential cost-effectiveness could outweigh its loss of efficacy. In that scenario, ICBT might be used in a stepped care model in which patients are first offered ICBT as a low-intensity intervention, reserving higher-intensity treatments that require specialist input (eg, face-to-face CBT) for more complex patients or those who do not benefit sufficiently from ICBT.^18^ Stepped care approaches are heralded as the ideal model of psychiatric service delivery^1^ but have rarely been evaluated.

We describe the trial protocol of a multicenter, single-blind, randomized clinical noninferiority trial aimed to investigate whether therapist-guided ICBT implemented within a stepped care model is noninferior to, and cost-effective compared with, the gold standard of face-to-face CBT for pediatric OCD. The main hypothesis is that the stepped care ICBT approach will be noninferior to gold-standard treatment (face-to-face CBT) in reducing clinician-rated OCD symptoms and will also be associated with lower resource use. As a secondary aim, the trial will explore whether the outcomes of ICBT differ between clinic-referred and self-referred patients.

## Methods

### Study Design

The study is a 2-site randomized clinical noninferiority trial for children and adolescents with OCD. Participants randomized to stepped care ICBT first receive ICBT for 16 weeks; patients classed as nonresponders at the 3-month follow-up are offered a course of face-to-face CBT for up to 12 weeks. Participants randomized to the gold standard treatment receive face-to-face CBT for 16 weeks; as in the stepped care group, patients classed as nonresponders at the 3-month follow-up are offered additional sessions of face-to-face CBT for up to 12 weeks. The full trial protocol is available in the Supplement.

The primary end point is 6 months after the end of the first course of treatment (6-month follow-up). Long-term effects will be investigated 1, 2, and 5 years after treatment completion. The trial design is graphically summarized in the Figure.

**Figure. zoi190527f1:**
[figure not shown]
CONSORT Flowchart Abbreviations: CBT, cognitive behavior therapy; ICBT, internet-delivered CBT.

The study was approved by the Regional Ethical Review Board in Stockholm, Sweden, and preregistered at ClinicalTrials.gov. The participants and their parents received verbal and written information about the study, including an informed consent form and an age-adapted information brochure specifically designed for the children and adolescents. The written consent procedure was witnessed by the clinician who provided the verbal information about the study. This trial protocol follows the Standard Protocol Items: Recommendations for Interventional Trials (SPIRIT) reporting guideline for clinical trials.^19^

### Study Sites

Study participants are assessed and treated at 1 of 2 specialist pediatric OCD clinics, located in Stockholm (Child and Adolescent Psychiatry Research Center) and Gothenburg (Sahlgrenska University Hospital), Sweden. Stockholm and Gothenburg are Sweden’s largest cities and have similar socioeconomic landscapes.^20^ The 2 clinics receive referrals from Child and Adolescent Mental Health Services within their respective regions but also accept referrals from other parts of Sweden.

### Participants

Consecutive patients referred to the 2 specialist clinics are assessed for eligibility. Participants can also find information about the study online and self-refer via a dedicated website. Eligible participants are offered a face-to-face appointment with a clinician for a full psychiatric assessment, including the administration of the Mini International Neuropsychiatric Interview for Children and Adolescents (MINI-KID),^21^ the Children’s Yale-Brown Obsessive Compulsive Scale (CY-BOCS),^22^ the Clinical Global Impression–Severity scale (CGI-S),^23^ and the Children’s Global Assessment Scale (CGAS).^24^ If suitable for the study, both the children or adolescents and their parents sign informed consent to participate during this visit. Participants receiving psychotropic medication are requested to continue using stable doses until the primary end point (6-month follow-up).

Inclusion criteria are as follows: primary diagnosis of OCD according to the *Diagnostic and Statistical Manual of Mental Disorders* (Fifth Edition)^25^; total score of 16 or greater on the CY-BOCS^22^; age between 7 and 17 years; ability to read and write Swedish; and daily access to a computer with an internet connection. Exclusion criteria are changes in psychotropic medication within the last 6 weeks prior to baseline assessment; comorbid diagnosis of organic brain disorders, global learning disabilities, autism spectrum disorder, bipolar disorder, or severe eating disorder; suicidal ideation; being housebound or in need of intensive or inpatient treatment; having completed a course of cognitive behavior therapy for OCD within the last 12 months (defined as ≥5 sessions including exposure and response prevention); and ongoing psychological treatment for OCD or an anxiety disorder.

### Randomization and Allocation Concealment

The allocation sequence is generated by an independent external party, the Karolinska Trial Alliance (KTA). The research team and the therapists who enroll the participants are not involved in the randomization or allocation process. Participants are randomized to either stepped care ICBT or gold-standard CBT through an online automated system for clinical trials. The allocation ratio is 1:1. Randomization is stratified by source of referral (clinician-referred or self-referred) and participant’s age (children [7-12 years] or adolescents [13-17 years]).

### Quality Control

This trial follows Good Clinical Practice (GCP) standards. All quality and safety aspects are regularly monitored by KTA (ie, case-by-case monitoring of informed consent, inclusion and exclusion criteria, source data quality, and adverse events).

### Blinding

Assessments of OCD symptom severity are conducted by a team of independent evaluators blind to treatment allocation at 3 different points: posttreatment, 3-month follow-up, and 6-month follow-up. To ensure blinding integrity, participants receive explicit instructions not to disclose which treatment they have received. After completing the assessment, the blind raters guess the participant’s group allocation and record whether the family has inadvertently revealed their group allocation.^26^ If participants inadvertently disclose the treatment allocation during the assessment, another blind assessor will rerate the participant’s CY-BOCS score based on the recording from the interview. We expect that the blind raters’ guesses on allocation will not be better than chance. The participants, therapists, and the project manager are not blind to treatment allocation. The 1-year, 2-year, and 5-year follow-ups are naturalistic (unblinded).

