#### Nonresponders

Participants in either group not meeting strict criteria for clinical response^30^ at the 3-month follow-up are offered up to 12 sessions of face-to-face CBT for OCD.^6^ This additional treatment is delivered between the 3-month and 6-month follow-ups. The content of the treatment is identical to the face-to-face CBT treatment, with the main focus on therapist-guided ERP.^28,29^ Individual adaptations are made to ensure optimal treatment dosage, including longer sessions or home visits as appropriate.

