Two types of analyses will be conducted on each of the 2 perspectives: a cost-effectiveness analysis and a cost-utility analysis. In the cost-effectiveness analysis, both number of responders and remitters at primary end point (6-month follow-up) will be used as the health outcome. We will use expert consensus criteria to define treatment response and remission.^30^ A responder is defined as at least 35% reduction on the CY-BOCS and a CGI-I score of 1 (very much improved) or 2 (much improved). Remission is defined as a score of less than or equal to 12 on the CY-BOCS and a CGI-S rating of 1 (normal, not at all ill) or 2 (borderline mentally ill). In the cost-utility analysis, the outcome will be quality-adjusted life years, according to international standards for cost-effectiveness analyses.^47,48^ Quality-adjusted life-years will be calculated using the area under the curve method.^49^ Costs will be estimated by appropriate regression analyses testing alternative link functions and distributions.^50^ Nonparametric bootstrapping with 5000 iterations will be carried out, pairing up differences in costs with differences in outcomes. As a global cost-effectiveness estimate, we will present the incremental cost-effectiveness ratio (difference in costs between the 2 groups divided by the difference in effect),^51^ as well as a visual presentation of cost-effectiveness planes. The time frames for the cost-effectiveness analyses will be from baseline to the 6-month follow-up, and from baseline to the 1-year follow-up.

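### The blinding repair after disclosure names only the CY-BOCS, although response and remission also need a CGI rating for which no blind rerating is stated

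*Protocol article*

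**What the plan says.** Blinding: "Assessments of OCD symptom severity are conducted by a team of independent evaluators blind to treatment allocation at 3 different points", namely posttreatment, 3 months and 6 months. Families are told not to reveal their treatment. Raters guess the allocation and record any disclosure. If a disclosure happens, "another blind assessor will rerate the participant’s CY-BOCS score based on the recording from the interview".

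Cost-effectiveness Analysis defines two composites, each with two parts:
- Response: "A responder is defined as at least 35% reduction on the CY-BOCS and a CGI-I score of 1 (very much improved) or 2 (much improved").
- For remission: a CY-BOCS score of 12 or less together with "a CGI-S rating of 1 (normal, not at all ill) or 2 (borderline mentally ill").

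The same section states that "both number of responders and remitters at primary end point (6-month follow-up) will be used as the health outcome".

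Secondary Outcome Measures lists CGI-S and CGI-I as clinician-rated outcomes in their own right.

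Nonresponders uses response at 3 months as a gate to further treatment before the primary end point: "Participants in either group not meeting strict criteria for clinical response" are offered additional sessions. That section cites the same consensus source as the response definition above.

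**The concern.** The repair covers one instrument, while the classifications need two. For a disclosing family, followed literally, the article pairs a blind CY-BOCS with a CGI rating that the repair does not reach. Three things use that CGI rating:
- the 6-month responder and remitter counts in the cost-effectiveness analysis;
- the secondary CGI analyses;
- the 3-month response classification, which comes before the primary measurement.

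These are the very cases that the plan has itself identified as unblinded. The gap is also separate from how well the CY-BOCS rerating is done, because even a perfect rerating leaves the CGI untouched.

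**Working it through.** **Is the gap in the text?** Setting the sections side by side:

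| Use | CY-BOCS part | CGI part | Blind rerating stated after disclosure |
|---|---|---|---|
| Primary outcome, 6 months | total score | none | yes |
| Response | reduction of at least 35% | CGI-I of 1 or 2 | CY-BOCS only |
| Remission | 12 or less | CGI-S of 1 or 2 | CY-BOCS only |
| Secondary CGI outcomes | none | CGI-S, CGI-I | none stated |
| Cost-utility (QALYs from the CHU9D) | none | none | not relevant |

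Statistical Analysis, Assessment Points and Outcome Measures add no rule that extends the rerating to the CGI.

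**When can the CGI change a classification?** Both composites are joined by *and*:
- Blind CY-BOCS criterion not met: the patient is not a responder (or remitter), whatever the CGI says.
- Blind CY-BOCS criterion met: the CGI decides.

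So the rerated CY-BOCS limits the damage. Only patients in the second group can be reclassified.

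**How large could it be?** The article gives no disclosure rate and no figure on this point to reproduce; its power statement concerns the CY-BOCS and is not involved. Inputs:
- N = 152 (Outcome Data);
- d, the share of families disclosing at a visit: assumed 5% to 15%;
- s, the share of those whose CGI-I crosses the boundary between 2 and 3 because the arm is known: assumed 20%;
- g, the share of those who meet the blind CY-BOCS criterion: unknown, at most 1.

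Families affected = N × d:
- 152 × 0.05 = 7.6, about 8
- 152 × 0.15 = 22.8, about 23

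With d from 2% to 20%, the count runs from 152 × 0.02 = 3.0 to 152 × 0.20 = 30.4, about 3 to 30.

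Changed response status = N × d × s × g. At the ceiling g = 1:
- 7.6 × 0.20 = 1.5
- 22.8 × 0.20 = 4.6

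That is about 2 to 5 patients per visit, or 1.5/152 = 1.0% to 4.6/152 = 3.0% of the sample. Any g below 1 lowers this in proportion. The planned 10% attrition lowers it again: 1.5 × 0.9 = 1.4 and 4.6 × 0.9 = 4.1.

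These figures refer to both arms together. The effect on the difference between arms depends on the direction of the shifts and their balance across arms, and the documents give neither.

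**The case against.** The strongest objection is that this argues from silence in a condensed article. The Blinding section does not say that the CY-BOCS is the *only* scale rerated, and the full protocol is in a Supplement that is not shown. A reader might infer that the CGI definitely stays with the assessor who knows the arm. The article does not say so, nor does it say expressly who rates the CGI. What stands is narrower: the article states a specific remedy, and its scope does not match the composites defined in the same article.

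Other stronger readings also go too far:
- *The primary result is biased.* The 6-month CY-BOCS is the score that the remedy covers. Any effect on it is indirect, through the 3-month classification and the additional course that follows.
- *The economic evaluation as a whole is compromised.* The cost-utility analysis uses QALYs and does not draw on the CGI.
- *Two to five patients will be misclassified.* That is a ceiling under unsourced assumptions.
- *The CGI is more open to bias than the CY-BOCS, and assessors expect less of internet treatment.* Neither statement has support in the article. The first is plausible for a global judgment; the second is conjecture.

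The existing safeguards also count. Disclosures are recorded and guesses are tested against chance, so the affected cases can be identified and examined. That makes the problem visible but does not supply a blind CGI rating.

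**Conclusion.** The point holds in a limited form. The stated repair is too narrow for the response and remission criteria and for the CGI outcomes, and no section shown closes the gap. It bears on secondary and cost-effectiveness outcomes and on the 3-month classification, and does not touch the blind rating of the primary outcome. The number of affected families is unknown: 8 to 23 per visit if 5% to 15% disclose. With a 20% CGI shift, at most 2 to 5 would change response status. The conclusion assumes that the CGI is rated at the same visit by the assessor to whom the family disclosed, and that the 3-month criteria are those defined for response elsewhere in the article, as the shared citation suggests. This is a cheap improvement, not a threat to the main conclusion.

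**What to change.** Amend the sentence in Blinding so that, after disclosure, the second blind assessor rates CGI-S and CGI-I as well as the CY-BOCS from the recording, with the baseline information needed to judge improvement. State that this rater's full set is used for response, remission and the CGI analyses at that visit. If the full protocol already provides for this, it is enough to say so in the article.

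The cost is a few extra minutes of a rater who is already planned; no new visits or staff are needed. The downside is that a CGI from a recording is slightly less informed than a live one. Trial Status places the primary results in the future, so 6-month ratings of disclosing families could still be completed from retained recordings before analysis. Classifications already acted on at 3 months cannot be undone this way.

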### Assessment Points

The assessments occur at predetermined points after randomization and are independent of the treatment progress. The primary end point is at 6-month follow-up. All clinician measures and self- and parent-reported questionnaires are administered at baseline, after treatment, and at 3-month, 6-month, and 1-year follow-ups. Self- and parent-administered measures of OCD symptom severity are also administered weekly during the first 16 weeks of treatment. Additional clinician follow-up assessments are conducted after 2 and 5 years via telephone. Changes in psychotropic medication and additional psychological treatment are monitored and documented throughout the study period.

### Planned Intervention

#### Internet-Delivered CBT

The BIP OCD intervention is a 16-week therapist-guided online self-help program consisting of 14 modules provided through a secure online site with double authentication.^12,13,14^ There are 2 age-adapted versions of the intervention, one for children aged 7 to 12 years and one for adolescents aged 13 to 17 years. The content of the intervention is presented in a varied and engaging manner, with reading material, films, animations, illustrations, and exercises adapted for the 2 age groups. The main treatment components are education, exposure with response prevention (ERP), and relapse prevention. An overview of the treatment content is presented in Table 1. Parents have separate accounts and receive parallel online guidance, including in-depth knowledge about OCD, the rationale for CBT and ERP, strategies to reduce family accommodation, and ways to incorporate positive reinforcement. During the treatment, families have regular contact with a dedicated therapist with expertise in treating patients with OCD. The therapist contact is provided through written messages in the online platform or, when necessary, telephone calls. The therapist responds to all activity on the platform and sends reminders to families in case of inactivity. After treatment completion, families continue to have access to all online material for a year (without therapist support). For an overview of BIP OCD, see https://vimeo.com/355965105/b3d5d1c439.^27^

**Table 1. zoi190527t1:** Overview of the Internet-Delivered CBT Treatment Modules

Module	Child or Adolescent	Parent
Education		
1	What is OCD?	OCD and explanation of the OCD circle
2	How to get rid of OCD	Rationale for CBT and treatment goals
3	What is exposure?	What is exposure and response prevention?
Exposure with response prevention		
4	Testing exposure	Parent strategies during exposure
5	Continue with exposure	More about exposure
6	When OCD affects the family	Reducing family accommodation
7	More exposure	Motivation and parent strategies
8	Deal with the obsessions	Think about obsessions during exposure
9	New steps with exposure	Evaluate the treatment
10	Using reexposure techniques	Using reexposure techniques
11	Perform a more difficult exposure	Perform a more difficult exposure
12	Reduce avoidance behaviors	Reduce avoidance behaviors
13	Exposure and treatment summary	Exposure and treatment summary
Relapse prevention		
14	Plan for the future	Plan for the future

Abbreviations: CBT, cognitive behavior therapy; OCD, obsessive-compulsive disorder.

#### Face-to-Face CBT

Participants in the gold-standard group receive face-to-face CBT based on validated protocols,^28,29^ including up to 14 sessions with a dedicated therapist delivered over 16 weeks (allowing for missed appointments due to illness or holidays). Parents are encouraged to participate in all the therapy sessions, but their attendance varies according to participant’s age and individual needs.

The treatment begins with 2 sessions of education about OCD and the treatment rationale. The main focus of sessions 3 to 12 is ERP and includes therapist-led exposure exercises. Between these sessions, participants are encouraged to practice ERP tasks on a daily basis. Sessions 13 to 14 include relapse prevention strategies and planning to reduce remaining OCD symptoms. Sessions are typically 1 hour long and conducted at the clinic, but can be longer or conducted outside the clinic or in the participant’s home, according to individual needs. All sessions are audiotaped and a random 20% of the sessions will be selected to ensure therapists’ adherence to the treatment protocol.

